#### Cognitive-behavioral therapy (CBT)

The PI tailored traditional cognitive therapy for depression [12] to the SAD population in developing the CBT for SAD protocol and its manual [30]. The treatment rationale addresses the role of environmental changes as well as cognitions and behavior in the onset and maintenance of seasonal depressive symptoms. CBT for SAD focuses on using traditional cognitive therapy elements of behavioral activation and cognitive restructuring to improve coping with winter. Behavioral activation is presented as a means to experience enjoyment during the fall/winter months by engaging in pleasurable activities. In addition to traditional cognitive restructuring of depressogenic thoughts, this treatment also identifies and challenges negative thoughts related to the winter season, low light availability (i.e., short days, cloud cover), and winter weather (e.g., cold temperatures, snow). To cope with subsequent winter seasons, each patient develops a personalized relapse-prevention plan, involving early identification of negative anticipatory thoughts about winter and of SAD-related behavior changes that occur early in his/her episode and using the skills learned to circumvent these prodromal signs of a SAD episode to prevent relapse and recurrence. Although cognitive therapy for depression is typically administered for 20 standard length (50-min) sessions over 16 weeks, SAD necessitates an intensified version. With winter lasting just 3 months, SAD patients may spontaneously remit with the arrival of spring if sessions were to be conducted over 16 weeks. Therefore, the protocol includes 12 longer (1½-h) sessions at a higher frequency (twice a week) over 6 weeks. Sessions are run in a small closed-group format with 4–8 participants per CBT group. Each group is led by a licensed PhD-level psychologist with a clinical graduate student co-therapist. All sessions are audiotaped to assess treatment adherence.

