### Sample size and statistical power

This RCT is designed to definitively test for a significant and clinically meaningful difference between CBT and LT on depressive episode recurrence during the next winter season (the primary endpoint). The true difference between CBT and LT (and the difference we observe in this more rigorous design) may be smaller than what was observed in the above pilot study. To determine sample size, the more conservative estimate of a 23% difference in recurrence was used, based on a worst case scenario assumption that all subjects who dropped out of the pilot studies at any time from randomization through the next winter follow-up would have evidenced a recurrence the next winter (52% in LT vs. 29% in CBT in the ITT sample). If the true difference is 23%, 80 participants per group (total *N* = 160) are required to provide 80% power to detect a significant difference in recurrence between CBT and LT with a 2-sided test and alpha = 0.05. With 80 participants per group, there is also 80% power to detect a 5-point difference in next winter continuous depression scores based on variance estimates from a worst-case scenario analysis of pilot data whereby pre-treatment scores were substituted for any missing next winter scores (14.3 ± 11.5 for CBT vs. 19.5 ± 11.5 for LT on the Structured Interview Guide for the Hamilton Rating Scale for Depression—Seasonal Affective Disorder Version).

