### Data analysis plan

The primary analysis is an intent-to-treat (ITT) analysis based on multiple imputation (MI) of missing next winter SIGH-SAD scores [39-41]. Imputed scores will be used to classify depression recurrence status for individuals who dropped out during the treatment phase, were withdrawn from protocol, or were subsequently lost to follow-up. Imputed values will be generated from multivariate normal models derived from subjects with next winter follow-up data, using baseline and post-treatment SIGH-SAD, HAM-D, and atypical scores, demographic variables (e.g., gender, race, age), and other baseline patient characteristics (e.g., presence of a comorbid axis I disorder, antidepressant medication status) as potential predictors. Separate models will be developed for the CBT and LT groups rather than including treatment group in the model as a predictor, because in the pilot study, baseline SIGH-SAD scores were negatively correlated with next winter scores in CBT and were positively correlated with next winter scores in LT. Outcomes for subjects with missing next winter data will be predicted from the models based on available data and a random component reflecting the residual distribution for the dependent variable. Ten data sets with different imputed values will be generated, and a dichotomous variable indicating recurrence status will be computed for each subject based on SIGH-SAD criteria. The difference between the CBT and LT groups in the proportions of subjects with a recurrence the next winter will be estimated for each of the ten data sets and the estimates will be combined using the inference methods for MI described by Little and Rubin [42]. SAS PROC MI and PROC MIANALYZE will be used to carry out the imputation and analysis. Sensitivity analysis will be conducted to determine the robustness of the results under alternative MI models and imputation methods, including best and worst case scenarios for each treatment.

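### CBT is given in closed groups and LT individually, but neither the sample size nor the described primary analysis allows for correlation within CBT groups; if there is any, the standard error is too small and 80% power is not assured

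*Protocol article*

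**What the plan says.** Under the heading Cognitive-behavioral therapy (CBT): "Sessions are run in a small closed-group format with 4–8 participants per CBT group". Each group meets for 12 sessions over six weeks with one psychologist and one student co-therapist. The section on therapist training and supervision has three lead therapists covering all the groups: the principal investigator and two community therapists.

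The Light therapy section describes a light box used daily, with duration adjusted for each participant according to weekly scores and side effects. No LT treatment groups are described. Randomization is of individuals, one to one.

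Under Sample size and statistical power, the assumed recurrence rates are "52% in LT vs. 29% in CBT in the ITT sample". The statement then reads "If the true difference is 23%, 80 participants per group" and says that these numbers "are required to provide 80% power to detect a significant difference in recurrence between CBT and LT". No ICC, design effect or inflation factor appears.

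Under Data analysis plan, the primary estimate is described as follows: "The difference between the CBT and LT groups in the proportions of subjects with a recurrence the next winter will be estimated". This is done in each of ten imputed data sets and the results are combined by multiple-imputation rules. The listed imputation predictors are depression scores, demographics and baseline characteristics; therapy group is not among them. The announced sensitivity analyses concern imputation only.

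**The concern.** Members of a closed group share sessions, fellow members and a therapist pair, so their later outcomes may resemble one another more than those of people in different groups. The protocol accepts that this kind of influence is plausible: the rationale for having no attentional control lists group dynamics, peer support and attention from the therapist among the possible sources of CBT's effect.

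If outcomes correlate within CBT groups, the variance of the CBT proportion exceeds the binomial variance. A test that ignores this rejects too often under the null hypothesis, and a sample size worked out under independence has less power than stated. Both would bear on the primary comparison of a trial presented as definitive.

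**Working it through.** **Inputs.** From Sample size and statistical power: 0.52 (LT) and 0.29 (CBT), difference 0.23, n = 80 per arm, two-sided alpha 0.05. From the CBT section: group size m of 4 to 8, so 80/8 = 10 to 80/4 = 20 groups, and about 13 at m = 6. The ICC is my assumption, taken over 0.02 to 0.10, because the article gives none.

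**Step 1: reproduce the stated figure under independence.**
- LT variance: 0.52 × 0.48/80 = 0.003120. CBT variance: 0.29 × 0.71/80 = 0.002574. SE under the alternative = √0.005694 = 0.0755.
- Pooled proportion 0.405. SE under the null = √(0.405 × 0.595 × 2/80) = 0.0776.
- Continuity-corrected: Φ((0.23 − 1/80 − 1.96 × 0.0776)/0.0755) = 80.7%, and 79 per arm are needed for 80%. Fisher's exact test gives 80.3% at 80 per arm.
- Uncorrected pooled: 84.9% (71 per arm needed). Unpooled Wald: Φ(0.23/0.0755 − 1.96) = 86.2% (68 per arm needed).

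The stated 80 per arm therefore matches an independent, continuity-corrected or exact calculation, with nothing set aside for clustering.

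**Step 2: add clustering in the CBT arm only.** Design effect DE = 1 + (m − 1) × ICC for CBT; LT stays at 1.
- Type I error of the unadjusted test = 2 × [1 − Φ(1.96/√((1 + DE)/2))].
- Wald power with a valid SE = Φ(0.23/√(0.003120 + DE × 0.002574) − 1.96).
- Continuity-corrected power = Φ((0.23 − 1/80 − 1.96 × SE₀)/SE₁), with DE applied to the CBT part of both SE₀ (null) and SE₁ (alternative).

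Results at m = 6:

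| ICC | DE | Type I error | Power, continuity-corrected | Power, uncorrected pooled | Power, Wald |
|---|---|---|---|---|---|
| 0 | 1.00 | 5.0% | 80.7% | 84.9% | 86.2% |
| 0.02 | 1.10 | 5.6% | 78.8% | 83.2% | 84.6% |
| 0.05 | 1.25 | 6.5% | 76.0% | 80.6% | 82.4% |
| 0.10 | 1.50 | 8.0% | 71.5% | 76.3% | 78.6% |

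Example, ICC 0.05: √(0.003120 + 1.25 × 0.002574) = 0.0796; 0.23/0.0796 − 1.96 = 0.93; Φ = 82.4%.

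At ICC 0.10 the type I error runs from 6.8% (m = 4) to 9.2% (m = 8).

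**Step 3: break-even.** At m = 6, power reaches 80% at an ICC of 0.007 (continuity-corrected), 0.057 (uncorrected pooled) or 0.081 (Wald).

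**Step 4: continuous score.** The article quotes "14.3 ± 11.5 for CBT vs. 19.5 ± 11.5 for LT" and claims 80% power for five points. Under independence, Φ(5/(11.5 × √(2/80)) − 1.96) = 78.5%. At ICC 0.05 and m = 6, Φ(5/(11.5 × √(2.25/80)) − 1.96) = 73.6%.

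None of these figures includes between-imputation variance, which would lower power further, or clustering by the three lead therapists, which I have not computed.

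**The case against.** **The ICC may be small.** The outcome is one winter visit about a year after a six-week group ended, with no continued CBT contact offered. At ICC 0.02 the type I error is only 5.6%, and at zero nothing changes. This stands, so the point has to be stated conditionally.

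**Power may still exceed 80%.** A reader might infer that the stated 80% is simply overstated. The documents do not support that as a flat claim. With an uncorrected test, 80 per arm gives 85–86% under independence, and at six per group power stays at or above 80% up to an ICC of about 0.06 to 0.08. Only under the continuity-corrected version does almost any positive ICC bring it below 80%. What stands is that 80% is not assured.

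**Much lower power figures are tempting.** Comparing the pilot's imputed rates (36.7% and 7.0%) with the worst-case rates suggests about 24% missing outcomes: (52 − 36.7)/(100 − 36.7) and (29 − 7)/(100 − 7). Removing 24% of the information as well would give 74%, 71% and 67% at the three ICCs. That is not supported. The worst-case rates already assume that "all subjects who dropped out of the pilot studies at any time from randomization through the next winter follow-up would have evidenced a recurrence", which cuts the pilot difference from about 30 points to 23, so a further 24% loss counts the same dropouts twice. Most of the fall, from 86% to 76%, would also be present at an ICC of zero and has nothing to do with clustering.

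**The variance may be specified elsewhere.** The data analysis section names neither a test nor a variance estimator, the article is condensed, and a statistical analysis plan may add a group term. That is fair for the analysis. It does not rescue the power statement, which is complete as given and has no allowance.

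**Only one arm is affected.** True; the design effect above is applied to CBT alone. Individual LT delivery is inferred from the description, not stated in those words.

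**Conclusion.** The point holds in conditional form. The design is partially nested, and neither the sizing nor the primary analysis as described allows for correlation within CBT groups. With any positive ICC, an unadjusted standard error is too small, whichever sizing formula was used. At six per group and ICCs of 0.02, 0.05 and 0.10, it is short by factors of about 1.02, 1.06 and 1.12 under the null hypothesis. The corresponding power ranges lie on both sides of 80%.

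These sizes rest on an assumed ICC range, equal groups of six, complete data, the article's 52% and 29%, and normal approximations. They do not show that the primary result will be wrong. They show that its error rate and power depend on a quantity the plan leaves out. The matter is inexpensive to settle.

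**What to change.** - In each imputed data set, estimate the risk difference with a variance that allows correlation within CBT group. Either use a cluster-robust variance with each LT participant as a singleton and small-sample degrees of freedom (there are only about 10 to 20 groups), or a partially nested model with a random group effect in CBT only. Combine by Rubin's rules.
- Let the CBT-arm imputation model reflect therapy group. Otherwise imputed scores carry no group effect and dilute the very correlation the variance is meant to capture.
- State how CBT participants who never joined a group are handled; treating them as singletons is the natural choice.
- Apply the same approach to the continuous next-winter scores.
- Restate the power over an ICC range such as 0.02 to 0.10, naming the test used. Keep the sample size.

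The cost is a change of analysis wording, a record of group membership in the analysis data set, a change to the CBT imputation model, a slightly wider confidence interval and a less favourable stated power. If the ICC proves close to zero, little is lost.

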#### Therapist training/supervision

In addition to the PI therapist, two experienced (≥ 4 years of practice beyond training at study outset) doctoral-level community therapists facilitate the CBT groups, supervised by the PI. Study therapists were recruited who had clinical experience with depression and experience in delivering CBT treatments, were able to commit to the study, and were willing to learn the study treatment. To train the therapists in the CBT for SAD protocol, the PI conducted formal training sessions with the two therapists together to review the session-by-session manual content and to review and discuss audiotapes of past CBT for SAD group sessions. During the first CBT group that each study therapist led, the PI reviewed audiotapes of all 12 sessions as they occurred. Supervision during the first CBT for SAD group consisted of 1.5-hour weekly meetings between the PI and the group of therapists and graduate student co-therapists involving a combination of (1) group discussion of general issues in therapy, participant progress, and the treatment protocol and (2) individual time where the PI provided detailed feedback on the prior two sessions to each therapist/co-therapist dyad. After each therapist completed the first intensely supervised CBT group, the PI provided continued supervision each year while CBT groups were ongoing by holding weekly 1-hour meetings with the group of therapists and co-therapists to discuss the sessions that occurred that week. The PI continued to listen to a sample (20%) of all CBT sessions conducted to monitor therapist adherence to the protocol and to offer detailed feedback on a subset of sessions. Study therapists are compensated for their time in training and attending supervision at the going rate for a clinical hour in VT and for their time in administering CBT at the going per patient group therapy rate in VT.

### Treatment integrity

Because there were no pre-existing adherence/fidelity measures for CBT for SAD, the NIMH Collaborative Study Psychotherapy Rating Scale (CSPRS; [name], personal communication, September, 2001), which measures the extent of specific therapist behaviors, was modified to measure adherence to our treatment protocols. CSPRS scoring procedures have been manualized [31], and adequate psychometric properties have been documented [32,33]. Original CSPRS items assessing specific CBT intervention components and nonspecific therapy aspects were retained with added items to assess psychoeducational and relapse-prevention components specific to our CBT manual. The language was modified to reflect group versus individual therapy. Items pertaining to clinical management were rephrased to reflect LT (as opposed to imipramine). A random sample (25%) of tapes is selected from each condition (CBT or LT) and session number and study therapist (in the case of CBT). Two trained clinical graduate students, blind to condition and session number, independently rate selected tapes. Inter-rater reliability and success at discriminating between the content of the CBT and LT conditions and between individual session numbers within the CBT condition will be computed. Patient’s treatment compliance is monitored by attendance and homework completion (for CBT) and LT diaries (for LT).

### Standardized information about ongoing and alternative treatments after study treatment ends

As a step to increase the likelihood that treatment in the interim is consistent with initial study treatment, standardized procedures are used for instructing participants with regard to treatment alternatives at the end of study treatment. When the treatment phase is complete in each study year, all participants receive a standardized letter, signed by the PI, encouraging them to keep up their study treatment and to pursue new treatments only if needed. Specifically, LT-treated participants receive a standard letter encouraging them to re-initiate daily LT upon onset of the first depressive symptom in the next fall/winter. The letter reiterates that LT participants can borrow our light boxes to use the next year as long as they have access to a professional to whom they can turn in the event of side effects and also lists contact information for LT manufacturers should they wish to purchase their own unit. CBT-treated participants receive a standard letter encouraging them to keep using the skills learned in the CBT for SAD treatment on their own. Both letters include the same, standardized safety net in providing contact information for local mental health centers and treatment providers should they require more formal treatment. This approach takes into account the ethical concern of not discouraging participants from getting needed treatment between post-treatment and the next winter follow-up while recognizing that we cannot ethically proscribe treatment and are accountable for directing them to resources.

### Formal follow-up assessments

Three formal, in-person follow-up assessments occur subsequent to study treatment completion: in the summer (i.e., the subsequent August), the next winter (i.e., January or February of the next wholly new winter season), and the second winter (i.e., January or February of the second wholly new winter season). All randomized participants are invited to attend follow-ups.

### Phone tracking of recurrences and retreatment

A blinded clinical graduate student telephones each participant twice in the interim between summer follow-up and the in-person next winter follow-up: once in October and once in December. The purpose of these brief phone contacts is to track any recurrences and any new treatments initiated. To track recurrences, DSM-IV-TR criteria for a major depressive episode on the SCID-CV are assessed for the interval between the present and last contact (i.e., formal assessment or phone call). To track retreatment, the caller asks, “Have you started any new treatments since (date of last contact) such as LT, talk therapy, or medications?” If the participant answers affirmatively, he or she is queried for specific details.

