The above analysis will be repeated using the following alternate recurrence definitions as secondary outcomes: (1) meeting SIGH-SAD recurrence criteria at the prospective next winter follow-up OR depression recurrence defined as any major depressive episode as assessed by the LIFE OR fulfilling DSM-IV-TR major depression criteria in the interim between summer and next winter as assessed by the October and December tracking telephone calls, (2) a recurrence on the next winter SIGH-SAD OR depression recurrence status as assessed by considering any new treatment reported in the interim between treatment endpoint and next winter follow-up (except for ongoing LT for LT participants and using CBT skills on their own without a therapist for CBT participants) as prima facie evidence of recurrence, and (3) the most encompassing and conservative definition of recurrence that defines a recurrence as fulfilling criteria (1) OR (2) above.

Secondary analyses will examine how potential modifiers influence the effects of CBT and LT on the primary outcome of next winter recurrence on the SIGH-SAD. Potential modifiers will include: (1) demographic variables such as sex, age, and race (White vs. minority); (2) baseline characteristics such as pre-treatment depression scores, axis I comorbidity, and baseline antidepressant medication status; and (3) complete or incomplete summer remission status in the interim, as ascertained by the SIGH-SAD at the summer follow-up. This will be done using logistic and linear regression analyses for dichotomous and continuous outcomes, respectively, and including the modifiers as well as their interactions with treatment in the models. Although the models are essentially the same as those fitted to the complete data for the purpose of imputation, for this analysis they will be fitted to the imputed data sets, and the Rao-Blackwell estimates of the effects of the modifiers will be obtained [43].

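### The blinded caller who rates interim depressive episodes also elicits treatment details that can disclose the arm, which weakens the blind for the phone-rated part of secondary recurrence definitions (1) and (3)

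*Protocol article*

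**What the plan says.** The section on phone tracking of recurrences and retreatment gives two tasks to one person. Under that section, "A blinded clinical graduate student telephones each participant twice in the interim between summer follow-up and the in-person next winter follow-up", in October and in December.

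- **Rating task.** "To track recurrences, DSM-IV-TR criteria for a major depressive episode on the SCID-CV are assessed for the interval between the present and last contact".
- **Treatment task.** "To track retreatment, the caller asks": "Have you started any new treatments since (date of last contact) such as LT, talk therapy, or medications". Then: "If the participant answers affirmatively, he or she is queried for specific details".

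The section on standardized information after study treatment sets out different advice by arm. LT participants are advised by letter to resume daily light when symptoms first appear in the following season, and the letter repeats that "LT participants can borrow our light boxes to use the next year", provided they have a professional to turn to for side effects. CBT participants are advised to go on using their skills by themselves. Both letters list outside treatment providers.

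In the data analysis plan, an episode found at the October or December call counts as a recurrence under secondary definition (1), together with the next-winter SIGH-SAD and the LIFE. Definition (2) treats new treatment as evidence of recurrence, "except for ongoing LT for LT participants and using CBT skills on their own without a therapist for CBT participants". Definition (3) is met when (1) or (2) is met. The primary outcome is recurrence on the in-person next-winter SIGH-SAD alone, given by a rater described as blind to treatment.

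**The concern.** A blinded rater is asked to collect the information most likely to break the blind. The question names LT as its first example. It is put in the months when an LT participant who follows the letter would be resuming light, and a yes leads to further questions. A participant who mentions a box borrowed from the study has identified the arm.

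If the student who hears this in October also calls in December, the December episode rating is no longer blinded for that participant. Episode criteria applied over the telephone need judgement, and those who have resumed light on the letter's advice will tend to be those with symptoms. The ratings most open to influence may therefore be the ones concerned.

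At stake is the phone-rated component of definitions (1) and (3). These definitions show whether the primary result survives a broader view of recurrence, so their ascertainment should be as well blinded as the primary's.

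**Working it through.** The article gives no figure for disclosure or for loss of blinding, so there is none to reproduce. The check is a reading of the sections side by side, followed by a count of who could disclose.

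**1. Does the word 'new' screen out resumed study LT?** Not reliably. Under the light therapy section, participants may keep the box through April and are asked to return it in May. The summer follow-up is in August. Someone who takes up light again in autumn has plausibly started it since the last contact.

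**2. What does each answer tell the caller?**

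| Answer | Information about arm |
|---|---|
| No new treatment | Little |
| Talk therapy or medication | Little; open to both arms |
| LT from an outside source | Suggestive; a CBT participant may also start LT |
| LT with a borrowed study box | Identifies the LT arm |

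**3. Which ratings are exposed?** The article describes the episode rating before the treatment question but fixes no order. If that order is kept, the October rating is made before any October answer, and what is exposed is the December rating by a caller who heard the October answer. If the order is reversed, the rating within the same call is exposed too.

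**4. How many could disclose?**

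- Inputs: 80 participants per arm (sample size section). Any LT use the next winter was reported by 4 of 36 LT patients in the pilot follow-up (Background).
- Rate: 4/36 = 0.111, agreeing with the stated 11%. The exact 95% interval is 3.1% to 26.1%.
- Expected number: 80 × 4/36 = 8.9, about 9. Over the interval: 80 × 0.031 = 2.5 to 80 × 0.261 = 20.9.

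This counts any LT use during the winter. Those who have resumed by the October call are at most this many. In the other direction, the article does not say whether pilot patients had the same letter and loan offer, so use could be higher here.

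**5. When does a tipped phone rating change a participant's status?**

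- Definition (1) = SIGH-SAD positive OR LIFE episode OR phone-rated episode.
- Definition (3) = definition (1) OR definition (2).

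A phone rating wrongly tipped towards an episode changes definition (1) only if the SIGH-SAD and the LIFE are both negative. A rating wrongly tipped away from an episode changes it only if no other component is positive. For definition (3), definition (2) must also be unmet. The LIFE rates depression week by week over the same interval from summer to next winter, so overlap is to be expected. The documents give no rate from which to estimate the share that remains.

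**The case against.** The strongest reply is that the calls need not reveal anything. The question covers new treatment only, details follow only a yes, a no says little, and most kinds of yes fit either arm. At the pilot rate about 71 of 80 LT participants (80 − 9) would have no LT use to report. This stands, and it limits the claim to what the answers can disclose.

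A reader might infer that the primary outcome is compromised because no sentence stops the caller from rating the winter visit. The documents do not support that. The SIGH-SAD rater is described as blind, a second blinded rater scores the tapes, and discrepancies of 5 points or more go to two further blinded raters, with corrected scores used in the analyses. Nothing says that the caller is the SIGH-SAD rater. Rules for assigning raters may also stand in the full protocol, which is not shown.

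A reader might also put a larger number on the bias. Using the 41% long-term LT use cited in the Background gives 80 × 0.41 = 32.8 participants. With an assumed 10% to 20% of ratings tipped, that is 0.41 × 0.10 = 4 to 0.41 × 0.20 = 8 percentage points. The 41% comes from a retrospective survey with a mean interval of 8.8 years, not from next-winter use. The tipping rate has no source in the documents, and the sum ignores the OR in definition (1).

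Nor do definition (2)'s exemptions oblige the caller to learn the arm. They can be applied later by someone who holds the allocation.

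What is left does not depend on silence. The article itself gives both tasks to the blinded caller.

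**Conclusion.** The concern holds in a limited form. As written, the tracking call can unblind the person who rates interim episodes, and an October disclosure could colour that person's December rating. The threat is to the phone-rated component of secondary definitions (1) and (3). An effect on the primary SIGH-SAD is possible only if the caller also rates that visit, which the document does not say.

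About 9 of 80 LT participants could disclose, assuming that next-winter LT use matches the pilot and that every user reports it. The number whose recurrence status would change is unknown and smaller, because a SIGH-SAD or LIFE recurrence already settles definition (1). The conclusion also assumes that the same student makes both calls, which is the natural reading of the section though not strictly fixed. The point is modest in size and cheap to remove.

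**What to change.** Amend the phone-tracking procedure as follows.

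1. In each call, complete and lock the episode rating before asking the treatment question.
2. Use a different blinded student for the December call. That student needs the date of the last contact, not the October answers.
3. Record treatment answers separately and keep them from all other raters.
4. Do not let a caller rate the same participant's later LIFE or SIGH-SAD.
5. Have someone who holds the allocation, such as the project statistician, apply the arm-specific exemptions of definition (2) afterwards from the recorded details.

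The cost is minor scheduling within the existing team of blinded raters, with no added contact.

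Passing the treatment question to the unblinded project coordinator is a tempting alternative but a worse one. New treatment itself counts as recurrence under definition (2), so unblinded ascertainment would move into definitions (2) and (3). It would also add up to 160 × 2 = 320 contacts.
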